#### Change in vaginal and urine microbiota

One polyester swap (FLOQSwab) is used to sample mid-vagina for microbial analysis and immediately been placed at – 80 °C until further processing. Urine is collected in a 50 mL collection tube using the clean catch method for women. Prior to voiding, the urethral meatus/urinary opening is cleaned with sterile water. Afterwards aliquoted into 10 mL fractions and immediately been placed at – 80 °C until further processing.

DNA is isolated from samples using standard DNA isolation kits and microbiota composition determined using 16S rRNA gene sequencing, which are performed at Centre for Clinical Research, North Denmark Regional Hospital. Microbiota composition is compared between groups and over time based on alpha- and beta-diversity measures, as well as changes in relative abundances of individual bacteria.

### Data collection

Data are collected electronically and stored in Research Electronic Data Capture (REDCap, Aarhus University), which is a secure online database. Demographic characteristics are collected from women included at baseline visit as follows: age, BMI, smoking, parities, age at menopause, years since breast cancer diagnosis, years since start at endocrine therapy, type of endocrine therapy.Study I: Symptom data are collected at baseline, after each treatment visit and 6 months after the initial treatment. Vaginal biopsy is collected at baseline visit and 6 months after the initial treatment. Vaginal and urine microbiota are collected at baseline visit, at each treatment visit, and 6 months after initial treatment (Table 2).Study II: Symptom data, vaginal biopsy, vaginal and urine microbiota are collected at baseline visit and one month after the last treatment (Table 3).Study III: Symptom data, vaginal biopsy, vaginal and urine microbiota are collected at one year follow-up visit which is scheduled one year after the completion of the last treatment in the study II, and one month after the single "booster" treatment.

**Table 2 Tab2:** The timeline of the treatment protocol for study I is summarized

	**Baseline**	**Treatment no. 1**	**Treatment no. 2**	**Treatment no. 3**	**Treatment no. 4**	**Treatment no.5**	**4–6 weeks after 5.treatment**
**Timepoint (weeks/months)**	0 weeks	4 weeks	8 weeks	12 weeks	16 weeks	20 weeks	6 months
**Eligibility criteria**	x						
**Informed consent**	x						
**Information from the patient record**	x						
**Questionnaires**	x				x	x	x
**Gynaecological examination**	x		x	x	x	x	x
**Vaginal biopsy**	x						x
**Vaginal and urine Microbiota**	x		x	x	x	x	x

**Table 3 Tab3:** The timeline of the treatment protocol for study II is summarized

	**Baseline**	**Treatment no. 1**	**Treatment no. 2**	**Treatment no.3**	**Treatment no.4/no. 5**	**4–6 weeks after the last treatment**
**Timepoint (weeks/months)**	0	4 weeks	8 weeks	12 weeks	-	4 months
**Eligibility criteria**	x					
**Informed consent**	x					
**Information from the patient record**	x					
**Questionnaires**	x					x
**Gynaecological examination**	x					x
**Vaginal biopsy**	x					x
**Vaginal and urine Microbiota**	x			x	x	x

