## Outcome measures

### Primary outcome

#### Vaginal dryness

Participant are asked to complete the 10-cm visual analog scale (VAS) ranging for 0 to 10, with higher score indicating worse vaginal dryness.Study I: Primary outcome is difference of vaginal dryness between baseline visit, and after third, fourth and fifth laser treatment.Study II: Primary outcome is difference in vaginal dryness four weeks after the last treatment between the laser group and the sham group.Study III: Primary outcome is vaginal dryness one year after the last laser treatment. Secondary outcome is the effect of one booster treatment on vaginal dryness.

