### Power calculation and statistical analysis

Considering the VAS score ranging for 0 to 10 for vaginal dryness as the primary outcome. In study one the sample size was calculated based on an expected mean 30% improvement on the VAS score for vaginal dryness from the third treatment compared to the fifth treatment. Aiming for a power of 90% and an alpha of 0.05 and a standard deviation of 2.9 was adopted [22], a sample size of 23 women were required. With an estimate loss of 20% participants during the five laser treatments, a total of 30 women will be included in study I. In study two the sample size was calculated based on an expected 30% improvement on the VAS score for vaginal dryness in the active laser group compared to the sham laser group. To achieve a power of 90% and an alpha of 0.05 with a standard deviation of 2.9 [22] it was determined that [22], a sample size of 21 women in each group was required. With an estimate loss of 20% participants during the second study, a total of 52 women will be included in study II, 26 in each group.

Statistical analyses will be performed using STATA. If the data followed a Gaussian distribution, the Student’s t-test will be used to test for differences between variable means. Otherwise, Mann Whitney's test will be used. For ordinal data from the questionnaires, Pearson’s χ^2^ and linear-by-linear tests will be performed. Paired test with one-way ANOVA will be used to evaluate change over time. Groups variables will be tested for change over time with two-way ANOVA (repeated measurements). A 2-sided *P*-value < 0.05 will be chosen as the level of statistically significance. Data are given as mean ± SD if they followed a Gaussian distribution; otherwise, median (range) are indicated.

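### The only pre-treatment dryness VAS is scheduled four weeks before the first laser, so Study I cannot separate untreated change from laser effect; Study II is not biased but names no baseline-adjusted comparison

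*Protocol article*

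**What the plan says.** The timepoint row of Table 2 (Study I) reads "0 weeks 4 weeks 8 weeks 12 weeks 16 weeks 20 weeks 6 months" for baseline, treatments 1 to 5 and the final visit. Baseline and first laser are thus four weeks apart. Table 3 (Study II) also puts baseline at 0 and treatment no. 1 at 4 weeks. In both tables questionnaires are marked at baseline and not at treatment no. 1.

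The Data collection text is compatible with this. For Study I: "Symptom data are collected at baseline, after each treatment visit and 6 months after the initial treatment". For Study II: "Symptom data, vaginal biopsy, vaginal and urine microbiota are collected at baseline visit and one month after the last treatment (Table 3").

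The outcomes differ in how they use baseline. Study I: "Primary outcome is difference of vaginal dryness between baseline visit, and after third, fourth and fifth laser treatment". Study II: "Primary outcome is difference in vaginal dryness four weeks after the last treatment between the laser group and the sham group". The Study I sample size rests on a different contrast, an "expected mean 30% improvement on the VAS score for vaginal dryness from the third treatment compared to the fifth treatment".

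The statistical section names Student's t-test or Mann-Whitney for differences between means, and a two-way repeated-measures ANOVA for change over time by group. It names no comparison adjusted for baseline.

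**The concern.** Study I has no control arm, so its baseline-to-post difference credits to the laser whatever else changes between the two readings. As scheduled, the first four weeks of that interval contain no laser at all. The article itself suggests why dryness might change then. Women enter because they are symptomatic, so some regression to the mean is plausible. Non-hormonal vaginal therapies are excluded for the month before baseline, whereas a fat-rich cream may be used during the study, so its use could begin after the baseline VAS. With no reading immediately before the first laser, this part of the change cannot be estimated or reported separately.

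In Study II the issue is precision rather than bias. A baseline VAS is collected, but the tests named do not adjust the post-treatment comparison for it. A second reading before treatment would make that covariate somewhat more informative.

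**Working it through.** **Inputs from the article.** SD 2.9, power 90%, two-sided alpha 0.05, 21 per group in Study II, 23 women in Study I before dropout, and visit times from Tables 2 and 3. **Assumptions.** The 30% improvement is read as 3 points on the 0–10 VAS. The correlation between a baseline and an outcome reading, r, is 0.3 to 0.7. The correlation between two baseline readings, rb, lies between r and 0.8. The size of the untreated change is also assumed. The article gives none of these.

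**1. The plan's own figure.** n per group = 2 × SD² × (1.960 + 1.282)² / d² = 2 × 8.41 × 10.51 / 9 = 19.6, so 20 by the normal approximation. The t-based solution is 20.65, so 21. The stated 21 reproduces.

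**2. Share of the interval before the first laser.** 4/16 = 25% to the treatment no. 4 visit (read as the assessment after treatment 3), 4/20 = 20% to the treatment no. 5 visit, and 4/26 to 4/24 = 15–17% to the final visit.

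**3. Study I with no laser effect.** SD of change = 2.9 × √(2(1 − r)), which is 2.90 at r = 0.5 and 2.25 at r = 0.7. The paired t-test with n = 23 has non-centrality √23 × drift / SD of change.
- Drift 0.5 point: non-centrality 0.83 and 1.07; significant in 12% and 18% of trials.
- Drift 1 point: non-centrality 1.65 and 2.13; significant in 35% and 53%.

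The nominal rate is 5%. In the third-versus-fifth contrast both readings follow the gap, so the drift cancels. It also shifts the third, fourth and fifth changes from baseline equally, so their order does not alter.

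**4. Study II with baseline adjustment.** The variance factor is 1 − r² with one baseline and 1 − 2r²/(1 + rb) with the mean of two. Multiplying 19.6 by the factor gives n per group for 90% power (normal approximation):

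| r | No adjustment | One baseline | Two, rb = r | Two, rb = 0.8 | Further variance cut from the second |
|---|---|---|---|---|---|
| 0.3 | 1 (20) | 0.910 (18) | 0.862 (17) | 0.900 (18) | 1–5% |
| 0.5 | 1 (20) | 0.750 (15) | 0.667 (14) | 0.722 (15) | 4–11% |
| 0.7 | 1 (20) | 0.510 (11) | 0.424 (9) | 0.456 (9) | 11–17% |

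At 21 per group and r = 0.5, power is 90.5% unadjusted, 96.5% with one baseline and 97.0–98.0% with two.

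The repeated-measures ANOVA does use baseline. With one reading before and one after treatment, its group-by-time test is a t-test on change, with variance factor 2(1 − r): 1.4, 1.0 and 0.6 at r = 0.3, 0.5 and 0.7. ANCOVA is lower throughout.

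**The case against.** Three stronger readings are tempting, and the document supports none of them.

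- A reader might set a 1-point drift against the roughly 2 points that n = 23 with SD 2.9 would detect (2.9² × 10.51 / 2² = 22.1, so 23) and call it half the target effect. The 23 was sized for third versus fifth treatment, from which the drift cancels. The 2 points are a back-calculation, stated nowhere, that takes 2.9 as the SD of paired differences.
- A reader might infer that an inflated before-after change would set the number of treatments in Study II. The article says only that this number depends on Study I results, and frames the question as three versus four versus five treatments. A constant offset does not alter that comparison.
- A reader might infer bias in Study II. Randomisation against sham balances the drift.

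Other objections stand in part. Entry requires discomfort and/or dyspareunia but no minimum dryness VAS, so the size of any regression to the mean is unknown. The cream may also be started after the first laser. A pre-laser VAS leaves later drift and placebo response uncontrolled. The second baseline adds nothing under an unadjusted t-test on the post-treatment VAS. Recruitment began in February 2023, so women already treated cannot supply the reading. A statistical analysis plan that is not shown may already adjust for baseline.

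The gap itself may not be meant literally. The Study I text counts six months from the initial treatment, whereas Table 2 counts from week 0. However, 20 weeks plus 4–6 weeks gives 24–26 weeks, so the table is consistent with itself; so is Table 3, where 12 plus 4 weeks gives the stated four months. If both visits fall on one day, the tables are wrong and need correcting.

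**Conclusion.** The point holds as a low-cost refinement and is not an error of calculation. On the printed schedule, four laser-free weeks lie inside every baseline-to-post difference in uncontrolled Study I and cannot be separated from laser effect. An untreated change of 0.5 to 1 point would raise the false-positive rate of that comparison from 5% to between 12% and 53%, at assumed correlations of 0.5 to 0.7. Whether such a change occurs is unknown.

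For Study II the conclusion concerns precision alone. Most of the gain comes from the baseline VAS already collected: 20 to 15 per group at r = 0.5, and 20 to between 18 and 11 over r = 0.3 to 0.7. A second reading cuts variance by a further 1–17%, and the upper end requires the two baselines to correlate no better with each other than with the outcome.

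**What to change.** - **Schedule.** For women not yet treated, add a dryness VAS at the treatment no. 1 visit, completed before the first laser, and mark it in Tables 2 and 3. If baseline and treatment no. 1 are in fact the same visit, correct the timepoint rows instead.
- **Study I.** Keep the primary outcome anchored to the baseline visit. Alongside it, report the week 0 to pre-laser change and the pre-laser to post-treatment change.
- **Study II.** Make the primary comparison an ANCOVA of the post-treatment dryness VAS on group and baseline dryness VAS, using the mean of the two pre-treatment values where both exist.
- **While editing.** Reconcile the Study I text, which has symptom data after each treatment visit, with Table 2, which marks no questionnaires at the treatment 2 and 3 visits. Also settle the origin of the six-month count.

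The cost is about a minute per woman at a visit that already takes place, with electronic capture, plus an edit to the tables and the statistical section. Women already treated will have no second reading, and the uncontrolled time after the first laser remains.

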### Randomization, blinding and informed consent

The women are e informed about the trial when they contact principal investigator. After signing of informed consent to participation, women are randomized in a 1:1 ratio to either laser group or sham group using an Internet-based randomization-program (REDCap, Aarhus University). Women are stratified by age, duration of prior endocrine treatment, and type of endocrine treatment. The participants in study II will be blinded to treatment allocation until the study has been completed.

### Side effects and adverse event

Vaginal laser therapy is associated with a low risk of complications. Most patients (97%) experience almost no or only mild discomfort in relation to the treatment [20]. The mild immediate symptoms after vaginal laser therapy are seen within the first two days and include burning sensation, itching, bruising and swelling [21]. The investigator will report to the Danish research ethics committees all suspected unexpected serious adverse reactions/events as soon as possible.

### Power calculation and statistical analysis

Considering the VAS score ranging for 0 to 10 for vaginal dryness as the primary outcome. In study one the sample size was calculated based on an expected mean 30% improvement on the VAS score for vaginal dryness from the third treatment compared to the fifth treatment. Aiming for a power of 90% and an alpha of 0.05 and a standard deviation of 2.9 was adopted [22], a sample size of 23 women were required. With an estimate loss of 20% participants during the five laser treatments, a total of 30 women will be included in study I. In study two the sample size was calculated based on an expected 30% improvement on the VAS score for vaginal dryness in the active laser group compared to the sham laser group. To achieve a power of 90% and an alpha of 0.05 with a standard deviation of 2.9 [22] it was determined that [22], a sample size of 21 women in each group was required. With an estimate loss of 20% participants during the second study, a total of 52 women will be included in study II, 26 in each group.

Statistical analyses will be performed using STATA. If the data followed a Gaussian distribution, the Student’s t-test will be used to test for differences between variable means. Otherwise, Mann Whitney's test will be used. For ordinal data from the questionnaires, Pearson’s χ^2^ and linear-by-linear tests will be performed. Paired test with one-way ANOVA will be used to evaluate change over time. Groups variables will be tested for change over time with two-way ANOVA (repeated measurements). A 2-sided *P*-value < 0.05 will be chosen as the level of statistically significance. Data are given as mean ± SD if they followed a Gaussian distribution; otherwise, median (range) are indicated.

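### Study II's two-group test switches between means and ranks on the observed distribution and does not use baseline VAS or the stratification factors: valid, but imprecise and without a fixed effect measure

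*Protocol article*

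**What the plan says.** The Study II endpoint, under Outcome measures (Vaginal dryness), is a contrast at one time point: "Primary outcome is difference in vaginal dryness four weeks after the last treatment between the laser group and the sham group".

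The section Power calculation and statistical analysis gives one rule for comparing two groups. With Gaussian data, the Student's "t-test will be used to test for differences between variable means". It continues: "Otherwise, Mann Whitney's test will be used". Neither test takes a covariate, and no criterion for judging normality is given. The same paragraph also says: "Groups variables will be tested for change over time with two-way ANOVA (repeated measurements". It covers all three sub-studies and does not say which test is primary for Study II.

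The trial already has the information that an adjusted analysis would need. Data collection says of Study II: "Symptom data, vaginal biopsy, vaginal and urine microbiota are collected at baseline visit and one month after the last treatment". Randomization, blinding and informed consent says: "Women are stratified by age, duration of prior endocrine treatment, and type of endocrine treatment". Baseline VAS is not among the stratification factors.

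**The concern.** A t-test estimates a difference in mean VAS, whereas Mann-Whitney compares ranks. These are different effect measures, and the stated rule picks one after the data have been seen. Dryness VAS is bounded at 0 and 10, so a switch is a realistic prospect. A reader of the results could not know in advance what the trial would report as its treatment effect.

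The second issue is efficiency. The planned evaluable number is only 21 per group. A baseline measurement of the same scale is usually the best available predictor of follow-up, and it costs nothing to use. Precision matters most if the true effect is smaller than planned. The article's own Discussion cites a sham-controlled trial of vaginal laser in breast cancer survivors that found no significant difference between groups.

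**Working it through.** **Inputs from the article:** SD 2.9; two-sided alpha 0.05; power 90%; 21 evaluable women per group; 1:1 allocation.

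**Assumptions:** The article gives a 30% improvement without stating its base; 3.0 cm (30% of the 10-cm scale) is taken. A smaller difference of 2.0 cm is shown for sensitivity. The baseline-to-follow-up correlation ρ is not given; 0.3, 0.5 and 0.6 are used. Baseline and follow-up SDs are taken as equal, and 2.9 as the SD of a single score.

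**1. The plan's own figure.** The normal approximation gives n = 2 × 2.9² × (1.960 + 1.282)² / 3.0² = 19.6, so 20 per group. The exact two-sample t-test (noncentral t) gives 20.65, so 21 per group, with 90.5% power at 21. The stated 21 is therefore reproduced by an unadjusted t-test at 3.0 cm. This supports reading that test as the intended Study II comparison.

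**2. Baseline adjustment alone.** The residual SD is 2.9 × √(1 − ρ²), and the variance falls by ρ². Power is by noncentral t at 21 per group.

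| ρ | Variance reduction | Residual SD | Power at 3.0 cm | Power at 2.0 cm |
|---|---|---|---|---|
| unadjusted | 0% | 2.90 | 90.5% | 58.7% |
| 0.3 | 9% | 2.77 | 92.9% | 62.8% |
| 0.5 | 25% | 2.51 | 96.5% | 71.2% |
| 0.6 | 36% | 2.32 | 98.3% | 77.8% |

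**3. Adding three stratification factors that predict nothing.** ANCOVA was simulated with baseline plus three non-prognostic binary factors, 21 per group. For ρ = 0.3, 0.5 and 0.6, power is about 90%, 95% and 97% at 3.0 cm, and about 58%, 67% and 73 to 74% at 2.0 cm. At ρ = 0.3 the gain over the unadjusted test is gone. This is a pessimistic case: the simulation balanced none of the factors, whereas stratified randomisation limits their chance imbalance, and any prognostic value would add power.

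**4. How much baseline imbalance matters.** The SD of the chance baseline difference at 21 per group is 2.9 × √(2/21) = 0.89 cm. In a follow-up-only comparison, only ρ times the imbalance carries over: 0.27, 0.45 and 0.54 cm for the three correlations. The t-test's standard error already allows for this.

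**5. The switch.** Null trials were simulated at 21 per group with VAS bounded at 0 and 10, using Shapiro-Wilk at 0.05 in each arm (an assumed criterion). Three assumed VAS distributions sent 8%, 55% and 80% of trials to Mann-Whitney. Type I error of the two-step procedure was 0.047, 0.057 and 0.046.

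**6. The repeated-measures ANOVA.** Study II has two symptom visits, so its group-by-time test is a change-score comparison with SD 2.9 × √(2(1 − ρ)) = 3.43, 2.90 and 2.59. Power is 78.9%, 90.5% and 95.5% at 3.0 cm, and 45.4%, 58.7% and 68.4% at 2.0 cm. This is below ANCOVA throughout, and below the follow-up-only t-test when ρ is under 0.5.

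**The case against.** An unadjusted test in a randomised trial is valid, and this is a condensed article, so a separate analysis plan may fix covariates and a normality criterion. At the effect that reproduces the sample size, power is already about 90%, and adjusting for baseline adds only 2 to 8 percentage points. All of this stands. It limits the size of the point but does not remove it, because the article states a method, and that method makes the effect measure depend on the data.

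Four stronger readings are tempting, and the documents do not support them:

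- **The plan allows three competing primary P-values.** The t-test and Mann-Whitney are alternatives under one rule. The two-way ANOVA is named for change over time, whereas the Study II primary outcome is a difference at one time point. The paragraph labels its tests loosely, but it does not offer the ANOVA for that outcome.
- **Baseline imbalance passes in full into the result.** Only the correlation times the imbalance does (step 4).
- **Ignoring stratification makes the standard errors too wide.** That follows only if age, duration and type of endocrine treatment predict dryness, and the article gives no evidence that they do. If they do, the error is conservative.
- **The normality check inflates type I error.** In simulation it stayed near 0.05.

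**Conclusion.** The point holds as one of efficiency and clarity, not validity. As stated, the Study II comparison has no fixed effect measure and does not use baseline VAS or the stratification factors.

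The gain from adjustment depends on a correlation that the article does not give. With baseline alone, and ρ from 0.3 to 0.6, it is 2 to 8 percentage points of power at 3.0 cm and 4 to 19 at 2.0 cm. With three added factors that prove non-prognostic, there is no gain at ρ = 0.3, and at 2.0 cm about 8 points at 0.5 and about 15 at 0.6. Both effect sizes are assumptions; 3.0 cm is the one that reproduces the stated 21 per group. The change is worth making because it needs no new data.

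**What to change.** For the Study II primary outcome, pre-specify one ANCOVA of dryness VAS at the post-treatment visit on treatment group, baseline VAS and the three stratification factors. Report the adjusted mean difference with its 95% confidence interval, whatever the observed distribution. Keep a rank-based or permutation test as a sensitivity analysis and remove the normality-driven switch for this outcome. State that the two-way repeated-measures ANOVA is not the primary analysis.

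The cost is a change of wording and a few degrees of freedom. All covariates are already collected. The one downside is the scenario in step 3: with weak correlation and non-prognostic factors, the adjusted analysis has about the same power as the unadjusted one.

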#### Sexual function

Participant are asked to complete the questionnaire Female Sexual Function Index (FSFI) for sexual function parameters; desire, arousal, lubrication, orgasm, satisfaction and pain (range 2–36, the threshold of 26.55 indicates sexual dysfunction) [16] and Sexual complaint screener – women (SCS-W) questionnaire addressing all domains of sexual dysfunction (range 0–60, higher score indicate increased symptom severity [17].

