#### Urinary symptoms

Evaluated by the questionnaire Urogenital Distress Inventory (UDI-6); irritative symptoms, obstructive/discomfort and stress symptoms (range 0–18, higher score indicate higher disability) [18] and International Consultation on Incontinence Questionnaire Female Urinary Tract Symptoms Sex (ICIQ-FLUTSsex) for evaluation of female sexual matters associated with their lower urinary tract symptoms (range 0–14, higher values indicating increased symptom severity) [19].

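### Pearson's chi-square and a linear-by-linear test are both named for ordinal questionnaire data with no rule for which decides; Pearson suits ordered scores badly, and neither test uses baseline

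*Protocol article*

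**What the plan says.** The statistical paragraph of the protocol article assigns tests by type of data. Means are compared by Student's t-test if the data are Gaussian. If they are not, "Otherwise, Mann Whitney's test will be used". A separate sentence covers the questionnaires: "For ordinal data from the questionnaires, Pearson"'s chi-square "and linear-by-linear tests will be performed". For change over time there is a paired one-way ANOVA, and also: "Groups variables will be tested for change over time with two-way ANOVA (repeated measurements)". The threshold is common to all: "A 2-sided *P*-value < 0.05 will be chosen as the level of statistically significance".

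The instruments are described under Sexual function and Urinary symptoms:
- FSFI, range 2-36.
- SCS-W, a "questionnaire addressing all domains of sexual dysfunction", range 0-60.
- UDI-6, range 0-18.
- ICIQ-FLUTSsex, for "female sexual matters associated with their lower urinary tract symptoms", range 0-14.

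The last three are described as running from lower to higher severity. Data collection (text and Table 3) places the study II questionnaires at baseline and after the last treatment.

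**The concern.** Pearson's chi-square treats score levels as unlabelled categories. Exchanging the women who scored 3 with those who scored 14 leaves the statistic unchanged. It therefore spreads its sensitivity over every possible pattern, when the question is whether scores are lower after laser than after sham. With many levels and few women, its reference distribution also fails.

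The linear-by-linear test in the same sentence does use the order. Two tests with very different properties are thus attached to the same data, and nothing says which result is the finding. Sexual function and urinary symptoms are named secondary outcomes, and the same data could be reported as a difference or as no difference. Neither test, as named, uses the baseline questionnaire.

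**Working it through.** **Inputs from the article.** Study II needs 21 women per group, and 26 are to be randomised. Alpha is 0.05, two-sided. The score ranges are those listed above.

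**The plan's own figure.** The basis is "To achieve a power of 90% and an alpha of 0.05 with a standard deviation of 2.9". Reading the 30% improvement as 3 points on the 0-10 scale (an assumption, since the reference is not stated):

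n per group = 2(1.960 + 1.282)² × 2.9² / 3² = 2 × 10.51 × 8.41 / 9 = 19.6

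The t-based solution is 20.65, so 21 as stated. The article gives no power figure for the questionnaires.

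**Expected counts on totals.** With equal arms and scores spread evenly over L levels, the expected count per cell is n/L.
- ICIQ-FLUTSsex, 15 levels: 21/15 = 1.40; 26/15 = 1.73.
- UDI-6, 19 levels: 21/19 = 1.11; 26/19 = 1.37.
- SCS-W, 61 levels: 21/61 = 0.34; 26/61 = 0.43.

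Uneven spread does not rescue this. With equal arms, a level reaches an expected count of 5 in each arm only if 10 women hold that score. Among 42 women at most four levels can do so (42/10 = 4.2), and among 52 at most five. Methods gives 60 women for study II instead of 52. At 30 per arm the counts would be 30/15 = 2.0, 30/19 = 1.6 and 30/61 = 0.5, so the conclusion is the same.

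**Behaviour of the two tests.** There were 4,000 simulated trials per setting with 21 per arm. Scores were rounded normals centred mid-scale, with SD = range/4.5 (assumption). Pearson uses the sum of (O − E)²/E. Linear-by-linear uses (N − 1)r² on 1 degree of freedom, where r is the correlation of score with arm. The table gives the percentage of trials significant at 5%.

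| Levels | Pearson, no difference | Linear-by-linear, no difference | Pearson, 0.8 SD | Linear-by-linear, 0.8 SD |
|---|---|---|---|---|
| 4 (assumed single item) | 3.1 | 4.8 | 39.2 | 63.9 |
| 15 | 1.8 | 5.0 | 10.7 | 71.2 |
| 19 | 1.3 | 5.1 | 6.4 | 70.3 |
| 61 | 0.0 | 4.6 | 0.1 | 72.2 |

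With 26 per arm and 0.8 SD, Pearson reaches 17.8, 10.8 and 0.3 on 15, 19 and 61 levels, against 79.7, 80.6 and 80.6 for linear-by-linear. Other mid-scale means and SDs, with the 2-36 score added in whole points, put Pearson at about 0-16% on totals with 21 per arm. A four-level item then gives about 44% against 65%.

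**How often the tests disagree.** The share of trials in which only linear-by-linear is significant is at least the difference between the two powers. From the table: 71.2 − 10.7 = 60.5%, 70.3 − 6.4 = 63.9% and 72.2 − 0.1 = 72.1%. A direct count under the other assumed means and SDs gives about 57-71%. For the four-level item the bound is 63.9 − 39.2 = 24.7%.

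**Baseline.** For a continuous score at 0.8 SD with 21 per arm, the noncentrality is 0.8 × √(21/2) = 2.59. Against a critical t of 2.02 this gives about 71-72% power. With an assumed baseline correlation of 0.5, adjustment raises the effect to 0.8/√(1 − 0.25) = 0.92 SD and the noncentrality to 2.99, or about 83%. Simulation gives 73-83% for the baseline-adjusted linear model, including the four-level item.

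**The case against.** The strongest reply is that the sentence must be read whole. A reader who stops at Pearson might infer that the plan would miss real questionnaire differences. It would not: the linear-by-linear test named beside it holds its 5% level and has about 70% power at 0.8 SD, close to a t-test on the same scores. That stands, and it limits the point.

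Four further replies:
- *Ordinal data may mean single items*, with totals going to the t-test or Mann-Whitney. The text allows this. Pearson is then usable, though clearly weaker, and the near-zero power figures apply only to undivided totals.
- *Repeated-measures ANOVA already uses baseline.* With two time points its group-by-time test compares change between arms. But the article does not say that it covers the questionnaires. If it does, it is one more analysis of the same outcome without precedence.
- *Precedence among secondary tests is usual analysis-plan content*, and that plan is not shown. This is fair for precedence alone. But choosing Pearson for ordered data is a positive statement in the article.
- *Pearson is conservative.* A reader might infer from the poor approximation that false positives are inflated. On totals it rejects 0-2% of the time under no difference. Even counting either test as decisive, the sums of the two error rates are at most 5.0 + 1.8 = 6.8% on totals and 4.8 + 3.1 = 7.9% on the four-level item.

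**Conclusion.** The point holds in a limited form. Pearson's chi-square is a poor choice for ordered scores at this sample size. It is named beside a test that would often contradict it, in about 57-72% of trials with a true 0.8 SD difference if totals are analysed. The article fixes neither the deciding test nor the level of the data. Neither test uses baseline; at an assumed correlation of 0.5 this costs roughly 12 percentage points of power on a continuous score (83% against 71%).

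These sizes rest on the assumed effect, mid-scale means and SDs, and 21 women analysed per arm. The low expected counts on totals do not depend on the assumed means or SDs. The consequence is ambiguity and lost precision on secondary outcomes. The documents do not support saying that the plan as a whole would miss real differences, or that the primary VAS comparison is affected. They also do not rank sexual function and urinary symptoms above the other secondary outcomes.

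**What to change.** Delete Pearson's chi-square for ordered scores and keep it for nominal variables. State for each questionnaire whether totals, domain scores or single items are analysed. Name one decisive between-group analysis for study II:
- totals and domain scores: a linear model of the follow-up score on arm, adjusted for the baseline score, reported as a difference with 95% CI;
- single ordinal items: proportional-odds regression adjusted for baseline, or the linear-by-linear test if a simple test is preferred.

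Say also whether the repeated-measures ANOVA covers the questionnaires and, if so, that it is supportive. The cost is analysis wording only. The baseline questionnaires are already collected, and no visit, measurement or sample size changes.
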